## **8.7 Blinding**

Since there is no comparator-arm, this trial will be conducted open-label where the treatment assignments are known to the investigator and the patient.

## **8.8 Storage Conditions**

Drug supplies must be kept in a secure, limited access storage area, in their original packaging and under the recommended storage conditions defined below. Legalon® SIL should be stored under 25°C. Storage temperature should be monitored by electronic min/max calibration certificated thermometers and documented once weekly on temperature log

The Principal Investigator should ensure the safe and secure IMP storage according to specifications provided by RPH and the use strictly in accordance with the study protocol.

## **8.9 Study Drug Accountability**

The principal investigator of each study site must maintain accurate and adequate records including dates, lot number, quantities received and individual usage.

IMP inventory and dispensing will be documented as follows:

-An IMP Inventory Form will be maintained and updated by the Site study staff; it will document the amounts received, dispensed, returned or unused.

-An IMP Accountability Form will be maintained and updated for all patients included by Investigator; it will document the amounts dispensed to each subject.

#### **8.10 Return or Destruction of Study Drug**

At the completion of the study, there will be a final reconciliation of drug shipped, drug consumed, and drug remaining. This reconciliation will be logged on the drug accountability form, signed and dated. Any discrepancies noted will be investigated, resolved, and documented prior to return or destruction of unused study drug. The Site study staff should return the partially used and unused study drug to RPH.

## **9 STUDY PROCEDURES**

### **9.1 Day – 14 (Screening visit)**

- Information of patient and Informed Consent
- Check for inclusion and exclusion criteria
- Medical History and prior concomitant medication
- Physical Examination:
  - Including blood pressure while sitting (right/left), pulse rate, temperature (degree Celsius), cardiac auscultation, chest auscultation, abdominal auscultation, brief neurological examination
- Concomitant medication
- Pregnancy test:
  - 10ml Heparin blood
- HCV-RNA, HIV-RNA
  - 10ml EDTA blood
- Full blood count, electrolytes (sodium, potassium), ASAT, ALAT, total and fractionated bilirubin, alkaline phosphatase, gammaGT, creatinine, albumin, total protein, INR, thyroid stimulating hormone (TSH)
  - 10ml Heparin blood
- Interleukin 28B genotype (if not available):
  - 10ml EDTA blood
- Plasma aliquot as backup-blood for potential later analysis
  - 10ml EDTA blood
- Accepted time window:  $\pm 3$  days

### **9.2 Day + 1 (baseline visit), immediately previous to iSIL administration**

- Check for inclusion and exclusion criteria
- Documentation of adverse events
- Concomitant medication
- Physical examination
  - Including blood pressure while sitting (right/left), pulse rate, temperature (degree Celsius), cardiac auscultation, chest auscultation, abdominal auscultation, brief neurological examination

- Safety laboratory: full blood count, electrolytes (sodium, potassium), ASAT, ALAT, total and fractionated bilirubin, gammaGT, total protein, alkaline phosphatase, creatinine, albumin, INR
  - 10ml Heparin blood
- HCV-RNA, HIV-RNA
  - 10ml EDTA blood
- CD3/4/8 count
  - 3ml EDTA blood
- Drug level of current ART
  - 10ml EDTA blood
  - Note the time-point (date, hour, minutes) of the last intake and the dosage (milligram) on the electronic CRF
  - Blood (10 ml) must be collected in EDTA solution vacutainer tubes. The tubes containing EDTA solution should be stored at +4°C. Tubes must be identified with the patient ID number and sample number as soon as blood has been collected
  - Blood samples must be brought to the laboratories without delay (maximum 30 min after blood collection).
  - Treatment of samples: centrifugation at 1500g for 10 min at +4°C. In a class II biohazard hood plasma (obtained after centrifugation) should be divided in three labelled tubes (of approximately 1mL each) ready for freezing at -80 ° C, within one hour after collection. If this deadline cannot be met, please keep the sample at 4° C until centrifugation and freezing
- Silibinin drug-level (Cmin (T0, pre-dose), Cmax (i.e immediately after the end of silibinin infusion) and one sampling at T4 (i.e. 4 hour after the end of silibinin infusion)
  - Blood (6 ml) must be collected in ACD (acid citrate dextrose) solution vacutainer tubes. The tubes containing ACD solution should be stored at +4°C. Tubes must be identified with the patient ID number and sample number as soon as blood has been collected
  - Blood samples must be brought to the laboratories without delay (maximum 30 min after blood collection).
  - Treatment of samples: centrifugation at 1500g for 10 min at +4°C. In a class II biohazard hood plasma (obtained after centrifugation) should be divided in three labelled tubes (of approximately 1mL each) ready for freezing at -80 ° C, within one hour after collection. If this deadline cannot be met, please keep the sample at 4° C until centrifugation and freezing.
- Plasma aliquot as backup-blood for potential later analysis
  - 10ml EDTA blood
- PBMC: only at the study site Zurich

- 10ml Heparin blood
- Administration of iSIL 20mg/Kg during 4 hours
  - Preparation of solution see below in the protocol
  - Vital parameters before, every 15min and after administration of iSIL
  - Documentation of side effects in the electronic CRF
  - If a central venous catheter (cvc) has to be placed due to poor condition of the peripheral veins:
    - The indication for cvc must be done by the principal-investigator
    - The correct placement of the catheter must be documented by X-ray or using the ECG-triggering method and documented in the electronic medical history
    - The insert site of the cvc must be checked every visit by the study nurse and signs of an infection must be documented in the CRF
    - If there are signs of an infection the cvc must be removed immediately and the catheter tip must be send to the microbiological laboratory
  - If a peripheral venous catheter has placed:
    - The Investigators are recommended to strictly adhere to the “Guidelines for the Prevention of Intravascular Catheter-Related Infections” (20)

### 9.3 Day 2 (visit 3)

- Documentation of adverse events
- Concomitant medication
- Physical examination
  - Including blood pressure while sitting (right/left), pulse rate, temperature (degree Celsius), cardiac auscultation, chest auscultation, abdominal auscultation, brief neurological examination)
- Safety laboratory: full blood count, electrolytes (sodium, potassium), ASAT, ALAT, total and fractionated bilirubin, gamma GT, alkaline phosphatase, creatinine, albumin, total protein, INR
  - 10ml Heparin blood
- HCV-RNA,
  - 10ml EDTA blood
- Silibinin drug-level T0 (pre-dose): only at the study sites Zurich and Lausanne
  - Blood (6 ml) must be collected in ACD (acid citrate dextrose) solution vacutainer tubes. The tubes containing ACD solution should be stored at +4°C. Tubes must be identified with the patient ID number and sample number as soon as blood has been collected

- Blood samples must be brought to the laboratories without delay (maximum 30 min after blood collection).
- Treatment of samples: centrifugation at 1500g for 10 min at +4°C. In a class II biohazard hood plasma (obtained after centrifugation) should be divided in three labelled tubes (of approximately 1mL each) ready for freezing at -80 ° C, within one hour after collection. If this deadline cannot be met, please keep the sample at 4° C until centrifugation and freezing.
- Administration of iSIL 20mg/Kg during 2 hours
  - Preparation of solution see below in the protocol
  - Vital parameters before, every 15min and after administration of iSIL
  - Documentation of side effects in the electronic CRF
- Accepted time window: same day

#### **9.4 Day 3 (visit 4)**

- Documentation of adverse events
- Concomitant medication
- HCV-RNA,
  - 10ml EDTA blood
- Administration of iSIL 20mg/Kg during 1 hour
  - Preparation of solution see below in the protocol
  - Vital parameters before, every 15min and after administration of iSIL
  - Documentation of side effects in the electronic CRF
- Accepted time window: same day

#### **9.5 Day 4 (visit 5)**

- Documentation of adverse events
  - use the electronic CRF
- Concomitant medication
  - use the electronic CRF
- Physical examination
  - Including blood pressure while sitting (right/left), pulse rate, temperature (degree Celsius), cardiac auscultation, chest auscultation, abdominal auscultation, brief neurological examination

- Safety laboratory: full blood count, electrolytes (sodium, potassium), ASAT, ALAT, total and fractionated bilirubin, gamma GT, alkaline phosphatase, creatinine, albumin, total protein, INR
  - 10ml Heparin blood
- HCV-RNA,
  - 10ml EDTA blood
- Silibinin drug-level T0 (pre-dose): only at the study sites Zurich and Lausanne
  - Blood (6 ml) must be collected in ACD (acid citrate dextrose) solution vacutainer tubes. The tubes containing ACD solution should be stored at +4°C. Tubes must be identified with the patient ID number and sample number as soon as blood has been collected
  - Blood samples must be brought to the laboratories without delay (maximum 30 min after blood collection).
  - Treatment of samples: centrifugation at 1500g for 10 min at +4°C. . In a class II biohazard hood plasma (obtained after centrifugation) should be divided in three labelled tubes (of approximately 1mL each) ready for freezing at -80 ° C, within one hour after collection. If this deadline cannot be met, please keep the sample at 4° C until centrifugation and freezing.
- Administration of iSIL 20mg/Kg during 1 hour
  - Preparation of solution see below in the protocol
  - Vital parameters before, every 15min and after administration of iSIL
  - Documentation of side effects in the electronic CRF
- Accepted time window: same day
- 

#### **9.6 Day 5 (visit 6)**

- Documentation of adverse events
- Concomitant medication
- HCV-RNA,
  - 10ml EDTA blood
- Administration of iSIL 20mg/Kg during 1 hour
  - Preparation of solution see below in the protocol
  - Vital parameters before, every 15min and after administration of iSIL
  - Documentation of side effects in the electronic CRF
- Accepted time window: same day

### **9.7 Day 6 (visit 7)**

- Documentation of adverse events
- Concomitant medication
- HCV-RNA,
  - 10ml EDTA blood
- Administration of iSIL 20mg/Kg during 1 hour
  - Preparation of solution see below in the protocol
  - Vital parameters before, every 15min and after administration of iSIL
  - Documentation of side effects in the electronic CRF
- Accepted time window: same day

### **9.8 Day 7 (visit 8)**

- Documentation of adverse events
- Concomitant medication
- HCV-RNA,
  - 10ml EDTA blood
- Administration of iSIL 20mg/Kg during 1 hour
  - Preparation of solution see below in the protocol
  - Vital parameters before, every 15min and after administration of iSIL
  - Documentation of side effects in the electronic CRF
- Accepted time window: same day

### **9.9 Day 8 (visit 9)**

- Documentation of adverse events
  - use the electronic CRF
- Concomitant medication
  - use the electronic CRF
- Physical examination
  - Including blood pressure while sitting (right/left), pulse rate, temperature (degree Celsius), cardiac auscultation, chest auscultation, abdominal auscultation, brief neurological examination

- Safety laboratory: full blood count, electrolytes (sodium, potassium), ASAT, ALAT, total and fractionated bilirubin, gamma GT, alkaline phosphatase, creatinine, albumin, total protein, INR
  - 10ml Heparin blood
- HCV-RNA
  - 10ml EDTA blood
- Silibinin drug-level T0 (pre-dose): only at the study sites Zurich and Lausanne
  - Blood (6 ml) must be collected in ACD (acid citrate dextrose) solution vacutainer tubes. The tubes containing ACD solution should be stored at +4°C. Tubes must be identified with the patient ID number and sample number as soon as blood has been collected
  - Blood samples must be brought to the laboratories without delay (maximum 30 min after blood collection).
  - Treatment of samples: centrifugation at 1500g for 10 min at +4°C. In a class II biohazard hood plasma (obtained after centrifugation) should be divided in three labelled tubes (of approximately 1mL each) ready for freezing at -80 ° C, within one hour after collection. If this deadline cannot be met, please keep the sample at 4° C until centrifugation and freezing.
- Plasma aliquot as backup-blood for potential later analysis
  - 10ml EDTA blood
- PBMC: only at the study site Zurich
  - 10ml Heparin blood
- Administration of iSIL 20mg/Kg during 1 hour
  - Preparation of solution see below in the protocol
  - Vital parameters before, every 15min and after administration of iSIL
  - Documentation of side effects in the electronic CRF
- Accepted time window: same day

#### **9.10 Day 9 (visit 10)**

- Documentation of adverse events
- Concomitant medication
- HCV-RNA
  - 10ml EDTA blood
- Administration of iSIL 20mg/Kg during 1 hour
  - Preparation of solution see below in the protocol
  - Vital parameters before, every 15min and after administration of iSIL

- Documentation of side effects in the electronic CRF
- Accepted time window: same day

### **9.11 Day 10 (visit 11)**

- Documentation of adverse events
- Concomitant medication
- HCV-RNA,
  - 10ml EDTA blood
- Administration of iSIL 20mg/Kg during 1 hour
  - Preparation of solution see below in the protocol
  - Vital parameters before, every 15min and after administration of iSIL
  - Documentation of side effects in the electronic CRF
- Accepted time window: same day

### **9.12 Day 11 (visit 12)**

- Documentation of adverse events
- Concomitant medication
- HCV-RNA,
  - 10ml EDTA blood
- Administration of iSIL 20mg/Kg during 1 hour
  - Preparation of solution see below in the protocol
  - Vital parameters before, every 15min and after administration of iSIL
  - Documentation of side effects in the electronic CRF
- Accepted time window: same day

### **9.13 Day 12 (visit 13)**

- Check for inclusion and exclusion criteria
  - use electronic CRF
- Documentation of adverse events
  - use the electronic CRF
- Concomitant medication
  - use the electronic CRF

- Physical examination
  - Including blood pressure while sitting (right/left), pulse rate, temperature (degree Celsius), cardiac auscultation, chest auscultation, abdominal auscultation, brief neurological examination
- Safety laboratory: full blood count, electrolytes (sodium, potassium), ASAT, ALAT, total and fractionated bilirubin, gamma GT, alkaline phosphatase, creatinine, albumin, total protein, INR
  - 10ml Heparin blood
- HCV-RNA
  - 10ml EDTA blood
- Drug level of current ART
  - 10ml EDTA blood
  - Note the time-point (date, hour, minutes) of the last intake and the dosage (milligram) on the electronic CRF
  - Blood (10 ml) must be collected in EDTA solution vacutainer tubes. The tubes containing EDTA solution should be stored at +4°C. Tubes must be identified with the patient ID number and sample number as soon as blood has been collected
  - Blood samples must be brought to the laboratories without delay (maximum 30 min after blood collection).
  - Treatment of samples: centrifugation at 1500g for 10 min at +4°C. In a class II biohazard hood plasma (obtained after centrifugation) should be divided in three labelled tubes (of approximately 1mL each) ready for freezing at -80 ° C, within one hour after collection. If this deadline cannot be met, please keep the sample at 4° C until centrifugation and freezing
- Silibinin drug-level (Cmin (T0, pre-dose), Cmax (i.e immediately after the end of silibinin infusion) and one sampling at T4 (i.e. 4 hour after the end of silibinin infusion)
  - Blood (6 ml) must be collected in ACD (acid citrate dextrose) solution vacutainer tubes. The tubes containing ACD solution should be stored at +4°C. Tubes must be identified with the patient ID number and sample number as soon as blood has been collected
  - Blood samples must be brought to the laboratories without delay (maximum 30 min after blood collection).
  - Treatment of samples: centrifugation at 1500g for 10 min at +4°C. In a class II biohazard hood plasma (obtained after centrifugation) should be divided in three labelled tubes (of approximately 1mL each) ready for freezing at -80 ° C, within one hour after collection. If this deadline cannot be met, please keep the sample at 4° C until centrifugation and freezing.
- Plasma aliquot as backup-blood for potential later analysis

- 10ml EDTA blood
- PBMC: only at the study site Zurich
  - 10ml Heparin blood
- Administration of iSIL 20mg/Kg during 1 hour
  - Preparation of solution see below in the protocol
  - Vital parameters before, every 15min and after administration of iSIL
  - Documentation of side effects in the electronic CRF
- Accepted time window: same day

#### **9.14 Day 13 (visit 14)**

- Documentation of adverse events
- Concomitant medication
- HCV-RNA,
  - 10ml EDTA blood
- Administration of iSIL 20mg/Kg during 1 hour
  - Preparation of solution see below in the protocol
  - Vital parameters before, every 15min and after administration of iSIL
  - Documentation of side effects in the electronic CRF
- Accepted time window: same day

#### **9.15 Day 14 (visit 15)**

- Documentation of adverse events
- Concomitant medication
- HCV-RNA,
  - 10ml EDTA blood
- Administration of iSIL 20mg/Kg during 1 hour
  - Preparation of solution see below in the protocol
  - Vital parameters before, every 15min and after administration of iSIL
  - Documentation of side effects in the electronic CRF
- Accepted time window: same day

### 9.16 Day 15 (visit 16, end of THISTLE)

- Documentation of adverse events
  - use the electronic CRF
- Concomitant medication
  - use the electronic CRF
- Physical examination
  - Including blood pressure while sitting (right/left), pulse rate, temperature (degree Celsius), cardiac auscultation, chest auscultation, abdominal auscultation, brief neurological examination
- Safety laboratory: full blood count, electrolytes (sodium, potassium), ASAT, ALAT, total and fractionated bilirubin, gamma GT, alkaline phosphatase, creatinine, albumin, total protein, INR
  - 10ml Heparin blood
- Pregnancy test:
  - 10ml Heparin blood
- HCV-RNA, HIV-RNA
  - 10ml EDTA blood
- CD3/4/8 count
  - 3ml EDTA blood
- Plasma aliquot as backup-blood for potential later analysis
  - 10ml EDTA blood
- PBMC: only at the study site Zurich
- Silibinin drug-level T24 (i.e 24 hour after the end of last silibinin infusion)
  - Blood (6 ml) must be collected in ACD (acid citrate dextrose) solution vacutainer tubes. The tubes containing ACD solution should be stored at +4°C. Tubes must be identified with the patient ID number and sample number as soon as blood has been collected
  - Blood samples must be brought to the laboratories without delay (maximum 30 min after blood collection).
  - Treatment of samples: centrifugation at 1500g for 10 min at +4°C. In a class II biohazard hood plasma (obtained after centrifugation) should be divided in three labelled tubes (of approximately 1mL each) ready for freezing at -80 ° C, within one hour after collection. If this deadline cannot be met, please keep the sample at 4° C until centrifugation and freezing.
- Accepted time window: at least one day after the end of iSIL administration

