|-------------------------------------------------|-------------------------------------------------------------------------------------------------------------------------------------------------------------------------------------------------------------------------------------------------------------------------------------------------------------------------------------------------------------------------------------------------------------------------------------------------------------------------------------------------------------------------------------------------------------------------------------------------------------------------------------------------------------|
| Main Exclusion Criteria:                 | 
Exclusion criteria:
 
 
• Contraindications to the study drug under study, e.g. known hypersensitivity or allergy to any ingredient of the study drug
 
• Patients in need of ART with HIV virological failure (<math>\geq 400</math> copies/ml) in the last 3 months
 
                                                                                                                                                                                                                                                                                                                           |
| Study Product, Dose, Route, Regimen:     | 
Intravenous Silibinin (iSIL) marketed in its esterified modification silibinin-C-2, 3-dihydrogen succinate and disodium salt as Legalon® SIL. All included patients will receive a lead-in therapy with iSIL in a dosage of 20mg/kg/day intravenously for 14 days once a day (day 1 to day 14). All study-subjects are treated outpatient.
 
On the end of the THISTLE study (day 15, i.e the day following the last iSIL administration) the subjects will be subsequently treated with standard of care triple therapy with telaprevir plus pegylated interferon and ribavirin (PR).
                                                          |

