score  $\geq 3$ ), an unfavourable interleukin 28 B genotype and a high baseline HCV viral load. The study results confirmed the efficacy of iSIL in a difficult-to treat patient group and underscored that iSIL could be a valuable treatment-option in patients not responding to PR (12). The potential role of iSIL as rescue therapy in patients not responding to previous combined therapy with PR and a HCV-specific PI was demonstrated by Biermer et al., 9 of the 13 responder patients are in the follow-up period: 3 of them achieved SVR24, 2 achieved SVR12, and 4 had a viral relapse (13). Recent reports also show the efficacy of iSIL in patients with HCV-reinfection after liver transplantation. After 14 days treatment of iSIL in a dosage of 20mg/kg all four patients showed normalization of liver enzymes and a significant decline of HCV-RNA with a mean log-reduction of 2.8 (14). Moreno et al. presented their data about the safety and the anti-HCV activity of a rescue therapy with iSIL in cirrhotic HIV-HCV co-infected individuals at the 19th conference on retroviruses and opportunistic infections (CROI) in 2012. They treated 4 individuals with previous partial response (PR) or relapses to PR with iSIL 20mg/kg for at least 14 days. Three patients started iSIL during PR and nitazoxanide (add-on strategy). Overall, therapy with iSIL led to negative HCV-RNA in 3 subjects and values  $<50$  IU/mL in the remaining. The period of mono-therapy with iSIL produced a time-dependent effect: the mean decrease of HCV-RNA was  $-2.5 \log_{10}$  IU/ml after 1 week and  $-4.62 \log_{10}$  IU/ml after 35 days. However, HCV-RNA rebounded in 4 patients after stopping iSIL. There were no significant adverse events related to iSIL and all patients maintained current antiretroviral therapy (ART) with undetectable HIV RNA (15).

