#### ***Primary endpoints:***

- Frequency of adverse events during iSIL treatment.
- Kinetics of the decline in HCV-RNA after 2 weeks of iSIL treatment (difference in IU/ml from day 1 to day 15, see flow-chart below).

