## 6 STUDY DESIGN AND COURSE OF STUDY

### 6.1 General Design

This study is a multicentre, open-label, interventional study including HCV-HIV co-infected individuals with chronic HCV-genotype 1 infection and documented previous null-response (NR) or partial-response (paR) to standard therapy with SOC and progressed liver fibrosis.

The overall study-duration is 15 days. The first part is the once a day administration of iSIL from day 1 to 14. Since the half-life ( $T_{1/2}$ ) of the administrated study-drug is very short (3 hours), the follow-up of the study-subjects is one day (day 15) and the final visit will be on day 15.

Subsequent to THISTLE (at day 15) we have the intention to include the study-subjects in the SHCS trial # 688. The trial # 688 will investigate the occurrence of HCV-resistance to the HCV-PIs during TT. The duration of the # 688 will contain 48 weeks with a follow-up of 24 weeks. Importantly, we plan to review the results from the THISTLE trial with the data from the SHCS # 688.

The estimated time frame is listed below:

- Submission to ethical committee (Zurich as lead ethical committee): November 2012
- Ethical approval: January 2013
- Swissmedic approval: February 2013
- First patient enrolled: April 2013
- Enrolment: April 2013 to December 2013
- Last patient enrolled: End of December 2013

All included patients will receive a lead-in therapy with iSIL in a dosage of 20mg/kg/day for 14 days followed by standard of care TT. As mentioned above, the follow-up period will contain for one day due to short half-life time of the administrated study-drug. Moreover, a prolonged follow-up period outside THISTLE trial is warranted due to the SHCS trial # 688.

The included patients are HCV-HIV co-infected SHCS participants with chronic HCV-genotype 1 infection and documented previous null-response (NR) or partial-response (paR) to standard therapy with SOC and in urgent need of treatment (i.e. METAVIR fibrosis score  $\geq 2$  or ISHAK fibrosis score  $\geq 4$  or fibroscan stiffness  $\geq 9.5$  kPa). As cut-offs for the fibroscan we used the ones proposed in a recent review by Castera et al (17). NR is defined as less than 2 log10 IU/ml decrease in HCV RNA level from baseline at 12 weeks. paR is defined as more than 2 log10 IU/ml decrease in HCV-RNA level from baseline at 12 weeks of therapy but detectable HCV-RNA at weeks 12 and 24.

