## **12 STATISTICS**

### **12.1 Statistical and Analytical Plans**

The analyses of the primary and secondary endpoints of this non-comparative study will be purely descriptive. The average decline of HCV RNA during the lead-in phase (day +1 to day +15) will be expressed in  $\log_{10}$  IU/ml using methods for left-censored data (Tobit regression) (18) in case of undetectable values are encountered and represents the primary efficacy analysis and will be performed in the evaluable patients. We will further report the percentages (with 95% CI) of patients achieving undetectable levels of HCV RNA at the various time points. We will also attempt to analyse factors associated with  $\log_{10}$  HCV RNA response with mixed effects models (19) taking into account all measured HCV values from day -14 to day + 15. In these models, slopes will be allowed to change at day+1 and day +15. Potential co-factors will be first assessed in univariable and bivariable models to detect interactions and collinearities. Relevant effect modifiers and confounders will then be included in multivariable models. The following co-factors will be considered: age, gender, IL28B genotype, BMI, CD4 values and HIV RNA. We will look at the potential co-factors in univariable models first and only include relevant confounding variables in the multivariable analysis. Safety analyses will be performed including all patients that received at least one dose of the study medication (Safety Population). Adverse events will be reported in percentages (with 95% CI) of patients experiencing an event (for clinical events and abnormal laboratory values considered clinically significant by the Investigator – this represent the primary safety analyses) or the percentages below/above 1x and 2x normal range limits for laboratory values.

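### The visit supplying the day-15 HCV RNA endpoint has an accepted window with no upper limit, in conflict with the fixed day 15 elsewhere in the protocol

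*Protocol*

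**What the plan says.** Section 9.16, the final visit, lists HCV RNA among its samples and closes with "Accepted time window: at least one day after the end of iSIL administration". No latest time is given. Each visit from day 2 to day 14 (sections 9.3 to 9.15) instead carries "Accepted time window: same day".

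The value from this visit feeds the primary efficacy endpoint, which section 5.1 defines as "difference in IU/ml from day 1 to day 15, see flow-chart below". Section 12.1 takes "The average decline of HCV RNA during the lead-in phase (day +1 to day +15") on the log10 scale as the primary efficacy analysis.

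Elsewhere the day is fixed. Section 6.1 says "the follow-up of the study-subjects is one day (day 15) and the final visit will be on day 15". The synopsis gives one day of follow-up and describes day 15 as the day following the last infusion. The study schedule gives the screening visit a tolerance and day 15 none.

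On what follows, the synopsis says that at the end of the study "the subjects will be subsequently treated with standard of care triple therapy", and section 4.4 reports from an earlier co-infected series that "HCV-RNA rebounded in 4 patients after stopping iSIL".

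**The concern.** The endpoint visit is the only visit after baseline whose accepted window has no upper end. A patient seen on day 17 or day 20 complies with section 9.16 and contradicts the synopsis, section 5.1 and section 6.1. Site staff following section 9 would have no deviation to report.

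This matters because a late sample can measure something other than the level at the end of iSIL. If the patient is untreated in the interval, rebound would understate the decline. If triple therapy has begun, its effect would overstate it. The study has one arm, so no control group would show a timing effect, and an in-window late value is not missing, so the missing-data rules in section 12.3 do not reach it. HIV RNA and CD4 counts are taken at the same visit under the same window.

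**Working it through.** The protocol states no figure that depends on this window, so there is none to reproduce. The check is a comparison of passages, followed by an illustration of scale.

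**Passages side by side**

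| Place | Timing of the final assessment |
|---|---|
| Synopsis, Study Duration | one day of follow-up, day 15 |
| Synopsis, Study Product | day 15 is the day after the last infusion |
| 5.1 | endpoint runs from day 1 to day 15 |
| 6.1 | final visit on day 15 |
| 9.16, silibinin T24 sample | 24 hours after the last infusion ends |
| 9.16, accepted window | one day or more after iSIL; no latest time |

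The last row is the exception. It is also the only explicit tolerance given for the visit.

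**What the half-life does and does not show.** Section 6.1 gives 3 hours. At 24 h the fraction of drug left is 0.5^(24/3) = 0.5^8 = 0.0039, or 0.4%. With once-daily one-hour infusions, a sample drawn just before the next infusion comes about 23 h after the previous one ended: 0.5^(23/3) = 0.0049, or 0.5%. The nominal day-15 sample is therefore close to an on-treatment trough. A late sample differs because one or more daily exposures are absent. The half-life says nothing about how fast the virus returns.

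**Illustration of scale.** Inputs: 20 evaluable patients (section 12.3); mean decline 3.02 with ±1.01 log10 (section 4.1), reading the ± as a standard deviation, which the protocol does not state.

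- 95% half-width = t(0.975, 19) × SD/√n = 2.093 × 1.01/√20 = 0.47, so 3.02 would have the interval 2.55 to 3.49.
- Shift in the mean = k × r/20, for k late patients each displaced by r log10 in the same direction.

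The protocol gives neither k nor r. Assumed ranges: k from 1 to 6, r from 0.5 to 3.

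| k | r | Shift in mean (log10) | Share of half-width |
|---|---|---|---|
| 1 | 0.5 | 0.025 | 0.05 |
| 2 | 1 | 0.10 | 0.21 |
| 4 | 1 | 0.20 | 0.42 |
| 6 | 1 | 0.30 | 0.63 |
| 6 | 3 | 0.90 | 1.9 |

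The range runs from negligible to larger than the sampling error. It depends wholly on assumptions, and with no late visits the shift is zero.

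**The case against.** The strongest reply is that day 15 is fixed so often elsewhere that the line in 9.16 is merely loose. Section 9.17 requires date and clock time for every sample, so late values can be identified, and HCV RNA is measured daily through day 14. The analysis is descriptive, with no hypothesis or success threshold (sections 12.1 and 12.2), so no decision rule would be tipped. All of this stands and limits the harm. It does not close the window, because 9.16 is a stated rule that sites will follow.

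Several stronger readings are tempting and are not supported:

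- A reader might infer that late values will be analysed as day 15. The protocol does not say so. Section 12.1 limits the decline and the mixed model to values up to day +15, which taken literally leaves later ones out, and a rule for assigning samples to visits may sit in an analysis plan not shown. Yet 12.1 also lets the slope change at day +15, which could be estimated only from later values, so the text is not clear.
- A reader might infer that triple therapy will contaminate the endpoint. The synopsis and section 6.1 place it after the end of the study, and section 4.5 speaks only of considering eligibility then. The natural order is final sample first. The text does not require that order, so the route remains possible but less likely than rebound.
- A reader might take the reported rebound as giving a rate. Section 4.4 gives no timing or size, and three of the four patients in that series started iSIL during other HCV treatment.
- A reader might extend the open window to the silibinin T24 level. That sample has its own 24-hour definition.

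Finally, section 5.1 refers to a flow-chart and Figure 2 is not shown, so a limit there cannot be excluded. If one exists, 9.16 conflicts with it too.

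**Conclusion.** The point holds as a conflict within the protocol. Section 9.16 accepts a final visit at any time from one day after iSIL, while the synopsis and sections 5.1 and 6.1 fix it at day 15. A late HCV RNA sample is therefore in-window for the primary efficacy endpoint although it may no longer describe the end of iSIL treatment.

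The size of any bias cannot be derived from the documents. It needs late visits, whose number is unknown, and a change in HCV RNA after the last infusion, whose rate is not given. The figures above show scale only. Given the nominal day, the recorded clock times, the daily values to day 14 and the descriptive analysis, this is a moderate to minor defect. It is worth correcting because it touches the primary endpoint and is simple to remove.

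**What to change.** 1. **Section 9.16.** Reconcile the window with the synopsis, 5.1 and 6.1. Give the HCV RNA sample an upper limit: the calendar day after the last infusion, at about 24 h, matching the T24 sample. Require it to be drawn before any first dose of triple therapy. This concerns only when blood is taken.
2. **Section 12.1.** State that a sample outside that window is not analysed as day 15. It either enters the model at its recorded time or is treated as missing, in which case section 12.3 applies. The daily values through day 14 then support the end-of-treatment estimate. Clarify what data the slope change at day +15 is meant to use.
3. **Sections 9.3 to 9.15.** State whether the daily HCV RNA samples are taken before the infusion. Only the day-1 visit says so (section 9.2). A pre-infusion day-14 value follows 13 infusions and not 14, so it supports the day-15 value without being identical to it.

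The cost is a few lines of text, with no added visit or assay. The downside is that an occasional late sample no longer counts as day 15.
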